Client-centredness of care	Adapted Client-Centred Care Questionnaire (CCCQ) [60]	PT, CG	T_1_, T_2_, and T_3_	-Descriptive analyses -T1: z test of proportions for group comparison, complete case analysis -T2: z test of proportions for group comparison, complete case analysis
Care experience	Integrated Care Patient-Reported Experience Measures (IC-PREMs) [61]	PT, CG	T_1_, and T_2_	-Descriptive analyses -T1: z test of proportions for group comparison, complete case analysis -T2: z test of proportions for group comparison, complete case analysis
Unmet care needs	Unmet Care Needs questionnaire	PT, CG	T_1_, T_2_, and T_3_	-Descriptive analyses - T1: z test of proportions for group comparison, complete case analysis -T2: z test of proportions for group comparison, complete case analysis
Caregiver strain	Modified Caregiver Strain Index (CSI) [62]	CG	T_1_, T_2_, and T_3_	-Descriptive analyses -T1-T2 (Treatment Effect): ANCOVA, complete case analysis -T2-T3 (Sustainability): ANCOVA, complete case analysis
Utilization of health and social services and associated costs	Institute for Clinical Evaluative Sciences (IC/ES), Health and Social Services Utilization Inventory (HSSUI) [63, 64]	PT, CG	T_1_, T_2_, and T_3_	-Descriptive analyses -T1-T2 (Treatment Effect): Mann-Whitney U test, complete case analysis, Hazard Ratio (95% CI) & Risk Difference (95% CI) for 30, 90 &180-day ED visits and hospital admissions -T2-T3 (Sustainability): Mann-Whitney U test, complete case analysis

*PT = patient; CG = caregiver, *T1 = baseline; T2 = 6-month; T3 = 12 months

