##### Cost of use of health and social services

The study will link participants to Institute for Clinical Evaluative Sciences (IC/ES) administrative databases to identify the use of emergency room visits, hospital admissions, use of family physicians, physician specialists, and home care services, and transfers to long-term care. In addition, the Health and Social Services Utilization Inventory (HSSUI) [63] will be used to measure the utilization of health and social services as reported by study participants and caregivers over the duration of the study. The HSSUI consists of questions about the respondent’s use of six categories of direct healthcare services: a) primary care; b) emergency department and specialists; c) hospital days; d) seven types of other health and social professionals; e) prescribed medications; and f) lab services. The data from the HSSUI will be used in combination with the IC/ES administrative data as a back-up in case we are unable to obtain IC/ES data at all three timepoints.

The six-month cost data will be derived from the product of “quantity” data reported on the HSSUI and 2015–2016 “price” data obtained by our team for the HSSUI [64]. The costs of use of health and social services will include the costs associated with delivery of the nurse-led intervention. This will form the basis of the cost-analysis, from a societal perspective that will compare changes in the costs of use of health and social services between participants in the intervention and control groups from baseline to 6- months, and from 6-months to 12-months post intervention. A complete copy of the HSSUI questionnaire is included as supplementary data (see Additional files 1 and 2). Table 1 provides an overview of the effectiveness evaluation, including the outcome, measures, group, and tiepoint for data collection.

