#### Analysis: effectiveness evaluation

Descriptive statistics will be used to summarize outcome values at baseline, 6 months and 12 months. Means and standard deviations will be used for continuous outcomes, and frequency and percentages will be used for categorical outcomes. Intention-to-treat analyses using analysis of covariance (ANCOVA) will be used to assess group differences in continuous outcomes from baseline to T2 in order to determine if the intervention was effective over the intervention period. The outcomes include: PRQ-2000, CESD-10, GAD-7, VR-12 PCS, VR-12 MCS, the PPC, CCCQ, and the IC-PREMs. The ANCOVA model will use the 6-month outcome value as the dependent variable, the group indicator as the independent variable and the baseline outcome value as the covariate. Model results will be expressed as mean group differences with accompanying 95% confidence limits. Quantile regression will also be used to examine the treatment effect over a broader range of values (beyond the mean) for the outcome variables. Assessment of group differences in continuous outcomes from T_2_ to T_3_ will be assessed using ANCOVA and will be aimed at assessing the sustainability of the intervention effects (see Table 1).

Z tests of proportions and McNemar tests will be used to assess changes within each group in the number of participants with acute care episodes and the number of acute care episodes from baseline to T_2_, and from T_2_ to T_3_ Acute care episodes include emergency department visits and hospital admissions. Risk difference (intervention risk – control risk) and accompanying 95% confidence limits will be calculated for 6 months for emergency department visits and hospital readmissions for 6 months. As was noted earlier, acute care episodes will be identified using administrative data from IC/ES, and self-reported data from the HSSUI. Due to the highly skewed nature of cost data, a non-parametric test will be used to compare the change in health and social service use and costs from baseline to T_2_ and from T_2_ to T_3_ for the two groups. Outliers are particularly common for certain healthcare costs such as hospital admissions, thus we will conduct a sensitivity analysis to assess the impact of outliers on the cost comparison.

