## Discussion

This paper described the design of pragmatic effectiveness-implementation trial of a nurse-led intervention (CAST) for older adults with MCC and depressive symptoms transitioning from hospital-to-home. The study will make four important contributions to the existing knowledge base. First, the study will assess both the implementation and effects of this transitional care intervention. Instead of focusing solely on whether the intervention ‘works’, the implementation evaluation results will be used to evaluate the sustainability of the intervention within each study site, and the potential for scalability to other jurisdictions. There is very little evidence regarding why certain transitional care interventions work in some settings or contexts but not in others [76]. This approach enables a focus on the complexity of interactions among the many contextual, macro-level factors that can affect implementation, which have been noted as highly relevant in determining both the outcomes and scalability of transitional care interventions [8, 28, 29]. Second, the study will include a cost analysis from a societal perspective – an outcome that has been overlooked in previous transitional care studies. This information will provide policy makers with a greater understanding of the ‘real world’ factors affecting implementation as well as the economic feasibility of integrating the intervention into usual care practice. Third, the study’s focus on older adults with MCC and depressive symptoms, a complex at-risk population that has been under-represented in transitional care evaluations, will enhance the generalizability of study results to this population. Fourth, the engagement of patients and caregivers in all aspects of the research, including the selection of patient- and caregiver-reported outcomes can inform future studies on outcomes that are important to assess from the perspective of patients and caregivers.

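### Costs are compared between arms only by a rank test on change, so no mean cost difference with an interval is planned, and the societal label goes beyond the items described

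*Protocol article*

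**What the plan says.** In the protocol article, *Analysis: effectiveness evaluation* gives skewness as the reason for the choice of test ("Due to the highly skewed nature of cost data") and states that "a non-parametric test will be used to compare the change in health and social service use and costs", for baseline to T2 and for T2 to T3. The last row of Table 1 names the test for both intervals; the second entry reads "T2-T3 (Sustainability): Mann-Whitney U test, complete case analysis". The one other cost comparison is that "we will conduct a sensitivity analysis to assess the impact of outliers on the cost comparison".

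Mean group differences with 95% limits are promised for the ANCOVA outcomes. Costs are not among them: "The outcomes include: PRQ-2000, CESD-10, GAD-7, VR-12 PCS, VR-12 MCS, the PPC, CCCQ, and the IC-PREMs".

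Under *Cost of use of health and social services*, cost is built as quantity from the service inventory (HSSUI) times unit price, with the cost of delivering the nurse-led intervention added. The inventory asks about the respondent's "use of six categories of direct healthcare services". The same section says of these data: "This will form the basis of the cost-analysis, from a societal perspective". The Discussion repeats that "the study will include a cost analysis from a societal perspective" and says policy makers will learn from it about the economic feasibility of building CAST into usual care.

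**The concern.** Whether CAST is affordable depends on total spend, which is mean cost times the number of patients. Mann-Whitney U asks a different question: whether a randomly chosen value in one arm tends to exceed one in the other. Skewness is a reason to choose the interval method with care. It does not change which quantity the decision needs.

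The gap matters because of how CAST is meant to work. It adds a delivery cost for nearly everyone in its arm and hopes to prevent a few expensive admissions. Small increases for many and large savings for few is the pattern in which ranks and means can separate.

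Two further points follow from the text. The T2-to-T3 change uses the T2 cost as its starting point, and that cost includes CAST delivery. And the societal label promises more than the listed items appear to contain, for an intervention that also acts on caregivers.

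**Working it through.** **Sample size, to fix the number of completers.** Inputs from *Sample size*: difference 6.5, SD 15.0, power 80%, alpha 0.05 (taken as two-sided), attrition 20%.

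- Per arm: 2 × (1.96 + 0.84)² × 15² / 6.5², which rounds up to 84. Then 84 / 0.8 = 105, or 210 in total.
- The t-based version gives 85 per arm and 214 in total. The stated 216 (3 × 72) agrees with this, so the sample size is not at issue.
- Completers: 216 × 0.8 / 2 = 86 per arm.

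The article gives no cost figures, so everything below on the size of the problem rests on assumptions.

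**What the test sees.** Assumed: background cost with mean $1,500; $12,000 per admission on average; both lognormal with log-scale SD 0.8; baseline cost containing one index admission and independent of later cost; 86 per arm; 2,000 simulated trials per scenario. The true mean difference is delivery cost + (CAST risk − control risk) × 12,000; for example 700 − 0.10 × 12,000 = −500. P is the probability that a CAST participant's value exceeds a control's.

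| Admission risk, control vs CAST | Delivery cost | True mean difference | Change score (planned): P, rejection | Follow-up cost (not planned): P, rejection |
|---|---|---|---|---|
| 30% vs 20% | 700 | −500 | 0.49, 5.8% | 0.58, 46% |
| 30% vs 20% | 1,200 | 0 | 0.51, 5.7% | 0.64, 88% |
| 30% vs 15% | 700 | −1,100 | 0.48, 7.1% | 0.57, 33% |
| 40% vs 30% | 700 | −500 | 0.49, 5.0% | 0.55, 22% |
| 30% vs 30% | 0 | 0 | 0.50, 4.9% | 0.50, 5.0% |

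On change scores, a saving of $1,100 and no difference at all look almost alike. On follow-up cost, ranks and means do diverge: P is above 0.5 while the mean shows a saving. That comparison is not the planned one.

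**Change against baseline adjustment.** For a mean-based analysis, the variance of a change-score comparison relative to an adjusted one is 2(1 − ρ)/(1 − ρ²) = 2/(1 + ρ), where ρ is the correlation of baseline with later cost. The documents give no ρ. The ratio is 2.00 at ρ = 0, 1.67 at 0.2 and 1.33 at 0.5. It does not carry over directly to a rank test.

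**T2 to T3.** Let S2 and S3 be service costs in the two six-month periods and D the delivery cost, which falls in the first because the intervention lasts six months. Suppose CAST changes nothing else.

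- Control change: S3 − S2.
- CAST change: S3 − (S2 + D).
- Difference between arms: −D.

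With the assumed D of $700, CAST appears $700 cheaper after the intervention although it did nothing. By the same algebra, any real saving in the first six months would count against CAST in the second comparison.

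**Perspective.** The items described are primary care, emergency and specialist care, hospital days, other health and social professionals, medications and laboratory services, plus programme delivery. Caregivers complete the inventory too, but that captures their own service use. Unpaid caregiver time, lost productivity and out-of-pocket spending are not in the description.

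**The case against.** A reader might infer that the planned test would tell policy makers CAST costs more when it saves money. The documents and the calculations do not support this. The reversals in the table are on follow-up cost, whereas the plan tests change. In a rerun on change scores under similar assumptions, P was about 0.49, on the side of the true saving. The lean was wrong in about 37% of trials, the same as for the mean change, and rejection was 5 to 6%. This objection stands, and the claim is limited to uninformativeness.

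It can also be said that a mean comparison would hardly be decisive at this size. With an assumed saving of about $1,000 and an SD of about $12,000, the standard error is 12,000 × √(2/86) = 1,830 and the 95% half-width about 1.96 × 1,830 = 3,590. In simulation the mean difference had the right sign in 72% of trials and a t-test rejected in 8%. This also stands. The gain is an estimate in money with an honest interval, not power.

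The plan is not empty on cost drivers. Descriptive means and SDs would be available by arm, and Table 1 plans hazard ratios and risk differences with 95% intervals for emergency visits and admissions. These help, but none is a between-arm cost difference with an interval. An unseen analysis plan could add one; the article nevertheless fixes the test and the label itself.

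Two more limits stand. The noise in the change score depends partly on whether the baseline window covers the index admission, and the look-back length is not stated. And it is tempting to say flatly that out-of-pocket costs are left out. The full questionnaire is in additional files not shown, so this cannot be confirmed.

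**Conclusion.** The point holds in a limited form. As written, the plan yields no between-arm difference in mean cost with an interval, which is what its stated economic purpose requires. This follows from the text and needs no assumed figures. Under the assumed costs, the planned test on change is close to uninformative about a mean saving of up to $1,100 (5 to 7% rejection against 5% with no effect). The T2-to-T3 comparison favours CAST by its own delivery cost when there is no effect, provided that cost is counted in the T2 figure, as the cost section reads. The societal label is not supported by the items described, subject to what the full questionnaire contains. Costs are a secondary outcome and the primary MCS analysis is untouched, so this is a change that should be made, not one that threatens the trial's main result.

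**What to change.** Make the cost analysis the between-arm difference in mean total cost over 0-6 months and over 0-12 months, with CAST delivery cost included, adjusted for baseline cost and site, with a bootstrap 95% confidence interval (or a gamma GLM). Using totals over 0-12 months removes the T2-to-T3 artefact. Keep Mann-Whitney U as a descriptive supplement and the outlier analysis as sensitivity. Change the last row of Table 1 and the cost sentences in *Analysis: effectiveness evaluation* to match.

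In *Cost of use of health and social services* and the Discussion, call the perspective one of health and social service cost, unless the full HSSUI also costs unpaid caregiver time, productivity and out-of-pocket spending. If it does, say so.

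The cost is analysis code and wording, with no new data collection. The downside is wide intervals around mean cost at this sample size and a narrower claim about perspective.

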### Participant flow, assessments and timeline

Independent Research Assistants (RAs) will assess participants at baseline within 2 weeks post-hospital discharge (T1) and again at 6 months (T2) and 12 months (T3) after baseline through a structured in-home interview. The study team will aim to complete all assessments at the participant’s place of residence, but completion by telephone is an option if participants prefer. Each assessment will take approximately 1–1 ½ half hours to complete. RAs with previous experience working in community-based settings will be trained in consent and data collection and management procedures. The Research Coordinator will meet with the RAs on a regular basis to address any questions and concerns and ensure consistency of approach across the three sites. The Research Coordinator will check the data at regular intervals during the data collection period in order to keep the number of errors and missing data as low as possible and gather maximum data for analysis. The flow of participants through the study phases will be presented using a flow diagram which conforms to the Consolidated Standards of Reporting Trials (CONSORT) guidelines for pragmatic trial reporting [39] (Fig. 2).

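### The older adults' T1-T2 service-use and cost comparison uses an unadjusted change score whose baseline probably includes the index hospital stay; a rank-based analysis adjusted for baseline would be more precise

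*Protocol article*

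**What the plan says.** All references are to the protocol article.

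- **Contrast.** Under Analysis: effectiveness evaluation, "a non-parametric test will be used to compare the change in health and social service use and costs from baseline"; the two periods compared between the groups are T1-T2 and T2-T3. The section on cost of use of health and social services agrees. The stated aim of its cost analysis is this: "compare changes in the costs of use of health and social services between participants in the intervention and control groups from baseline to 6- months".
- **Test.** The utilization row of Table 1, which covers patients and caregivers, gives "T1-T2 (Treatment Effect): Mann-Whitney U test, complete case analysis". No baseline covariate is named. The same row adds hazard ratios and risk differences for emergency visits and admissions.
- **Cost window and content.** "The six-month cost data will be derived from the product of “quantity” data reported on the HSSUI" and unit prices. The inventory's categories include "c) hospital days; d) seven types of other health and social professionals".
- **Timing.** Eligibility criteria: older adults are recruited from a hospital at each site. Participant flow, assessments and timeline: "Independent Research Assistants (RAs) will assess participants at baseline within 2 weeks post-hospital discharge (T1", T1 being the label for baseline. Randomization and blinding: allocation follows collection of the baseline data.
- **Other continuous outcomes.** The ANCOVA models the 6-month value, with "the group indicator as the independent variable and the baseline outcome value as the covariate".

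**The concern.** Every older adult in the trial has just left hospital when T1 is measured. A T1 value that looks back over the same length of time as the six-month cost data would therefore take in the index stay, or at least its last part. That cost was settled before randomisation, and CAST cannot change it. A T2-minus-T1 score carries its variation between people into the outcome.

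The plan avoids this for its continuous scales by using baseline as a covariate, but not for use and cost. At stake is the precision of a secondary comparison that the article treats as important. Lower use of expensive services is part of the hypothesis (Research questions), and the societal cost analysis is listed among the trial's four contributions (Discussion). An imprecise contrast could give an inconclusive cost result. Both arms would also show a fall from an index-stay peak, which is easily misread as improvement.

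**Working it through.** **1. The plan's own figure.** The only sample size is for the VR-12 MCS: difference 6.5, SD 15.0, alpha 0.05 (taken as two-sided), power 80%, attrition 20%.

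n per arm = 2 × (1.960 + 0.842)² × 15² / 6.5² = 83.6, so 84. Then 84 / 0.8 = 105 per arm, 210 in total. A t-based calculation gives 85, then 107 per arm, 214 in total. The stated 216 is reproduced closely. It says nothing about cost, for which no power is stated. Completers per arm: 216 × 0.8 / 2 = 86.4, about 86.

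**2. Variance of the two contrasts.** Let k = SD(T1) / SD(T2) and ρ = the T1-T2 correlation. Relative to comparing the T2 value alone:

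- change: 1 + k² − 2ρk
- baseline-adjusted: 1 − ρ²
- difference: (k − ρ)², never negative.

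In this linear setting, change is therefore never the more precise contrast. The direction needs no cost assumption; the size does. Example with k = 1, ρ = 0.3: change 1.40, adjusted 0.91, ratio 1.40 / 0.91 = 1.54.

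Power below uses 86 per arm and the standardised effect that gives the T2-only comparison 80%: d = 2.802 × √(2/86) = 0.427. The document gives neither k nor ρ; these are assumed ranges.

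| k | ρ | variance, change | variance, adjusted | power, change | power, adjusted |
|---|---|---|---|---|---|
| 1 | 0.1 | 1.80 | 0.99 | 55% | 80% |
| 1 | 0.3 | 1.40 | 0.91 | 66% | 84% |
| 1 | 0.5 | 1.00 | 0.75 | 80% | 90% |
| 1 | 0.7 | 0.60 | 0.51 | 95% | 98% |
| 1.5 | 0.3 | 2.35 | 0.91 | 45% | 84% |
| 1.5 | 0.7 | 1.15 | 0.51 | 74% | 98% |
| 2 | 0.3 | 3.80 | 0.91 | 30% | 84% |

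Change is worse than the T2 value alone only if ρ < k/2.

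**3. Simulation with an explicit index stay.** All cost inputs are assumed: 86 per arm; log-normal costs with log-SD 1.2; mean 6-month cost 7,000, reduced by 40% under CAST; mean other baseline cost 5,000; an independent index-stay cost averaging 5,000, 10,000 or 15,000 (log-SD 0.9); latent correlation 0.1 to 0.7; 1,000 trials per scenario (simulation SE at most √(0.25/1000) = 1.6 points).

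| Analysis | Power |
|---|---|
| Mann-Whitney, 6-month cost alone | 75-79% |
| Mann-Whitney, change including index stay | 17-59% |
| Mann-Whitney, change excluding index stay | 47-91% |
| Rank ANCOVA, T1 value (index stay included) as covariate | 74-86% |

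With no true effect, rejection was 5-6% for all four.

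**4. Simulation without a separate index-stay term.** 86 per arm, follow-up median 5,000, log-SD 1.2, 40% reduction. With baseline median 5,000-12,000, baseline log-SD 0.5-1.0 and r 0.1-0.5, Mann-Whitney on change had 24-83% power against 76-88% for rank ANCOVA. A further run of 16 scenarios with r up to 0.7 gave 26-93% against 75-96%, with rank ANCOVA higher in all 16. At r = 0.7 and baseline median 5,000 the gap is small: 90-94% against about 96%.

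**5. Linear ANCOVA on raw cost.** In the same kind of setting it had only 51-70% power. In one set of 18 scenarios it was less powerful than Mann-Whitney on change in 8. Example: baseline median 5,000, log-SD 0.5, r = 0.3 gives 74% for change and 54% for linear ANCOVA.

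**The case against.** Four objections deserve weight.

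- **The index stay is not shown to be in the T1 value.** A reader might infer that baseline always contains it. The article gives neither the T1 look-back nor the handling of that stay, and the questionnaire is in additional files not at hand. This stands: the premise is a plausible inference from a six-month window. Even so, the precision result in step 2 does not depend on it; only the size of the loss does. With the index stay excluded and latent correlation 0.7, change did well (90-91%).
- **Hospital use is analysed elsewhere.** A reader might infer that the trial could not detect fewer admissions. Table 1 and the analysis section provide hazard ratios and risk differences for emergency visits and admissions, and these do not use change. This stands for those events. It does not cover hospital days, other services or total cost.
- **Part of the utilization row is unaffected.** Caregivers need not have had an admission, and neither window of the T2-T3 comparison contains the index stay. This stands.
- **Nothing is invalid.** Randomisation protects the test, and null error is about 5%. This stands: the point is efficiency in a secondary outcome, not bias.

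The planned outlier sensitivity analysis does not answer the point, because it leaves the subtraction in place.

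**Conclusion.** The point holds as one of precision, limited to older adults' T1-T2 comparison of service use and cost. The plan fixes an unadjusted change score in three places. A baseline-adjusted comparison of the follow-up value uses the same data more efficiently, and rank ANCOVA was more powerful than Mann-Whitney on the corresponding change score throughout steps 3 (index stay included) and 4.

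The size is conditional. At equal SDs the variance ratio is 2/(1 + ρ): 1.54 at ρ = 0.3, 1.33 at 0.5 and 1.18 at 0.7. It grows if T1 is more variable than T2, as an included index stay would tend to make it. That much of the power is lost is therefore one possible outcome, not an established one, since the document gives no cost mean, SD, correlation or effect. The simulated index stay was also taken as independent of later cost, which favours a large loss.

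**What to change.** In the cost section, the effectiveness analysis section and the utilization row of Table 1, for older adults' T1-T2 comparison:

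- Make the outcome service use and cost accrued from baseline/randomisation to T2.
- Compare arms with a rank-based analysis adjusted for the T1 value (rank ANCOVA) in place of Mann-Whitney on change. Do not carry over the linear ANCOVA written for the scales; on raw cost it can be weaker than the planned test.
- Keep T1 values and change scores as description only.
- In the same edit, a clause giving the T1 look-back and whether the index stay is counted would settle the inference above.

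The T2-T3 comparison, caregivers' own use, and the hazard ratios and risk differences need no change on this account.

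Cost: no new data; one model replaces one test. Like Mann-Whitney, rank ANCOVA does not give a cost difference in money, so nothing the planned test would report is lost.

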### Research questions

The study addresses three research questions:
What is the effect of a new, nurse-led hospital-to-home transitional care intervention compared to usual care on health outcomes and costs for older adults with MCC and depressive symptoms and their caregivers?How is the new care transition intervention adapted and implemented in diverse settings?What is required to sustain and scale up the intervention?

It is hypothesized that, compared to usual care, the intervention will result in improvements in health outcomes for older adults with MCC and depressive symptoms while reducing the utilization of expensive healthcare services (e.g., hospitalization).

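### The outlier check on costs is attached to a rank test on cost change, so capping outliers would almost never alter it, and mean cost goes unexamined

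*Protocol article*

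**What the plan says.** The section on analysis of the effectiveness evaluation justifies the cost test by skewness: "Due to the highly skewed nature of cost data, a non-parametric test will be used to compare the change in health and social service use". The same sentence applies this test to cost too, over both periods (T1 to T2, then T2 to T3). Table 1, in the row on utilization and costs, names the test for both periods; for the second it reads "T2-T3 (Sustainability): Mann-Whitney U test, complete case analysis". Costs are not in the list of ANCOVA outcomes, and that row of Table 1 has no quantile regression. No between-arm difference in mean cost is named. Means and standard deviations are planned only as descriptive summaries of continuous outcomes.

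The next sentence gives the reason for a sensitivity analysis, "Outliers are particularly common for certain healthcare costs such as hospital admissions". It then commits to the check itself in these words: "thus we will conduct a sensitivity analysis to assess the impact of outliers on the cost comparison". It gives no definition of an outlier, no rule for handling one, and no quantity on which the impact is to be measured. The section on research questions states the hypothesis that CAST improves health outcomes "while reducing the utilization of expensive healthcare services (e.g., hospitalization").

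**The concern.** As the text stands, the cost comparison to which the check refers is the Mann-Whitney test. The skewness that led to a rank test also makes the outlier check uninformative on that test, because ranks have already removed the size of the extreme values.

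The article plans a cost analysis from a societal perspective and says in its Discussion that it will inform policy makers about economic feasibility. The quantity that scales to a budget is the mean cost per person, and a few long admissions can dominate that mean. If the main and sensitivity rank results agree, a reader may conclude that the cost finding does not hinge on a few expensive patients. Agreement after capping does not support that conclusion for mean cost.

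The other common way to run such a check is to repeat the test without the outliers. That can change the result, but for a poor reason: it removes people because of something that happened after randomisation and that the intervention is meant to prevent.

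**Working it through.** **Inputs from the article.** Sample size 216, 1:1 allocation, 20% attrition, significance level 0.05, Mann-Whitney U on change in cost. The article states no figure for the cost comparison, so its only related figure is the sample size, reproduced here to fix the number analysed:

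- n per arm = 2 × (1.96 + 0.84)² × 15.0² / 6.5² ≈ 84, so 168 in total; 168 / 0.8 = 210, within 3% of 216.
- Analysed per arm: 216 × 0.8 / 2 ≈ 86.

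**Step 1: size does not enter the test.** U counts the cross-arm pairs in which one value exceeds the other, with ½ for ties. Any strictly order-preserving change to the analysed scores leaves every pair, and so p, unchanged. In simulation, multiplying the largest change score by 10 changed p by exactly 0. This needs no assumption about costs.

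**Step 2: capping acts only through ties.** With 86 per arm there are 86 × 86 = 7,396 pairs, and the SD of U is √(7,396 × 173 / 12) ≈ 327. Capping the top 5% of 172 change scores ties about 9 values. They form at most 4 × 5 = 20 cross-arm pairs, each moving U by at most ½, so U moves by at most 10, or 10 / 327 ≈ 0.03 SD. This bound does not depend on the cost distribution either.

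**Step 3: simulated capping.** Cost and admission inputs are assumptions; the article gives none.

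| Handling (86 per arm) | Shift in p | 0.05 verdict changed |
|---|---|---|
| Cap change score; admissions 35% v 25% | median 0.002 | 0.15% |
| Cap raw costs, then subtract; 35% v 25% | median 0.02 | about 1.6% |
| Cap change score at 1st/99th percentile; 30% v 30%, 30% v 15%, 40% v 20% | at most 0.0024 | at most 0.1% |
| Cap change score at 1.5 IQR fences; same three scenarios | up to about 0.15 | 0.2-1.2% |

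**Step 4: the same capping on the mean.** In 4,000 simulated trials (35% v 25%, lognormal costs, mean admission cost 12,000), capping the top 5% of follow-up costs moved p by a median of 0.002. The mean difference went from -1,173 to -937, a change of 1 - 937 / 1,173 = 20%. This run used follow-up cost and not change. It shows the contrast: the rank test hardly moves while the mean does.

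**Step 5: exclusion.** In 3,000 trials per scenario (background costs lognormal with log-mean 7.5 and log-SD 0.8; admission costs 9.5 and 0.8), dropping change scores outside the 1.5 IQR fences gave:

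| Admissions | Significant, all kept | Significant, outliers dropped | Verdict changed |
|---|---|---|---|
| 30% v 30% | 0.053 | 0.055 | 4.8% |
| 30% v 15% | 0.358 | 0.146 | 24% |
| 40% v 20% | 0.555 | 0.336 | 25% |

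Of those dropped, 89-96% had been admitted, and 36-56% of all admitted participants were dropped. With 35% v 25%, exclusion changed the verdict in 5.6-8.8% of trials.

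On the mean difference in change, dropping the outer 5% took -1,107 to -739, a loss of 1 - 739 / 1,107 = 33%. Further exclusion rules gave losses of roughly 35-60%. Milder rules and other assumed costs can fall outside that range on either side.

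**The case against.** The strongest reply is that the article fixes neither a definition of outliers nor their handling, and that such detail for a secondary cost analysis commonly sits in an analysis plan, which is not shown. That is fair, and the absence of those details is not the point. The point is the pairing that is stated: for this rank test, one usual handling is nearly empty and the other selects on the outcome. A plan that moved the check to mean cost would already have made the change proposed here.

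Three stronger readings are tempting, and the document does not support them:

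- A reader might infer that the check will show robustness whatever the data are. It will not, because exclusion changes the result. Capping raw costs before taking the difference also alters ranks, and log-compressing costs first changed the verdict in 5-11% of simulated trials, although logs turn the contrast into a ratio. Besides, a rank result that looks stable is stable for what it tests.
- A reader might infer that outliers will be dropped. The article never says so.
- A reader might infer that admissions are the main source of outliers. They are given as an example.

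It also stands that any exclusion would sit beside a retained main analysis, that emergency visits and admissions are analysed directly with risk differences and hazard ratios, and that Table 1 labels the cost analysis complete case, while the analysis section attaches intention-to-treat to the ANCOVA outcomes. The harm is therefore limited to what the sensitivity analysis can tell the reader.

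**Conclusion.** The concern holds in a limited form. The outlier check is poorly matched to the one cost test named. If outliers are capped or shrunk, the conclusion almost never changes (0.1-1.6% of simulated trials across the handlings that cap at percentiles or fences), and nothing is learned about mean cost. If they are excluded, the check does respond, but it conditions on an outcome after randomisation that CAST is hypothesised to reduce and tends to shrink a real difference.

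Invariance to the size of the change scores and the 0.03 SD bound for a 5% cap at 86 per arm do not depend on assumed costs. All simulated percentages, including the 35-60%, rest on assumed lognormal costs and admission risks and show direction and order of size only. The choice of the Mann-Whitney test as the main cost analysis is not in question. Cost is a secondary outcome, so this is a worthwhile improvement and not a threat to the trial's main conclusion.

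**What to change.** Keep the Mann-Whitney test as the main cost analysis and replace the sensitivity sentence with:

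> The effect of extreme costs will be assessed on the between-arm difference in mean change in cost (bootstrap 95% CI), as observed and with costs winsorised at the pooled 95th and 99th percentiles; all participants with cost data are retained and none is excluded because of a high cost.

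The wording refers to participants with cost data so that it agrees with the complete-case label in Table 1. The cost is one sentence and a few lines of code. The price is a sensitivity result that may look less stable than the rank test suggests.
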